#### Comorbid disorders

2.6.4

Comorbid personality disorders are assessed with the Structured Clinical Interview for DSM-5 Personality Disorders (SCID-5-P) (50). The SCID-5-P is a semi-structured DSM-5-based interview which assesses the presence of personality disorders. It is supplemented with a screenings questionnaire to shorten the duration of the interview. Interrater reliability of the former version was excellent (51).

Comorbid syndrome disorders are assessed with the Structured Clinical Interview for DSM-5 Syndrome Disorders (SCID-5-S) (52). This semi structured interview aims to assess DSM-5 syndrome disorders. Two studies confirmed the psychometric properties (53, 54).

#### Social functioning, quality of life and economic evaluation

2.6.5

To study the effects of DBT-PTSD on social functioning, we use the Work and Social Adjustment Scale (WSAS). The WSAS measures impaired functioning due to a disorder and contains five items/domains (work, home management, social leisure activities, private leisure activities and maintaining close relationships). Reliability and validity were demonstrated (56). We operationalize functional recovery with a score of ≤10 on the Work and Social Adjustment Scale.

We assess health-related quality of life with the EQ-5D-5L (55), a self-report questionnaire with excellent psychometric properties (57). It consists of five dimensions: mobility, self-care, usual activities, pain/discomfort and anxiety/depression. Each dimension has five levels: no problems, slight problems, moderate problems, severe problems and extreme problems. We will calculate Quality Adjusted Life Years (Qalys) with the EQ-5D-5L using the Dutch tariff of Versteegh et al. (58).

The TiC-P is a reliable self-report questionnaire that assesses healthcare consumption and productivity loss for clients with a psychiatric disorder (59). The TiC-P has a recall period of three months and aims to facilitate estimation of direct medical costs and productivity costs in paid and unpaid work. It is widely used in the Netherlands for economic evaluations in mental health. The TiC-P captures for instance duration, intensity and type of (follow-up) mental health and other treatment in the waiting period, during the intervention and after discharge, as well as (emergency) admissions to the hospital, before and after discharge.

#### Client perspectives and individual symptom trajectories

2.6.6

With a qualitative semi-structured interview, we study clients’ experiences with DBT-PTSD. With open questions clients are asked about subjects like, changes they experienced during and after treatment, factors they perceived as helping or hindering the treatment process and their suggestions for improvement. Interviews will take 60 to 90 minutes and will be audiotaped and afterwards verbatim transcribed.

We use the DBT-PTSD diary to assess symptom trajectories and the individual differences herein between clients. The DBT diary was developed and provided by Bohus and colleagues in the Central Institute for Mental Health in Mannheim, Germany. As part of treatment, clients keep a digital daily diary during the twelve weeks of treatment. Items in this diary include among others, PTSD intrusions, sleep, suicidality, problem behavior, happiness, time spent on therapeutic assignments and frequency of exposure assignments. Items vary from nominal, (yes/no), ordinal (5-point Likert scale) to continuous.

#### Baseline screening

2.6.7

We use the Screener for Intelligence and Learning disabilities (SCIL), which is a valid and reliable screening questionnaire developed to detect an intelligence quotient of ≤ 84, indicated by a cut-off score of 19 or lower (60). Out of consideration for clients’ wellbeing and the validity of the results, clients are offered to stop the interviews or complete only part of the measurements when they have a SCIL score <20, show difficulty understanding the measurements, or seem too distressed.

### Data management

2.7

Two independent research nurses coordinate data collection. They are the only ones that have access to client information in combination to the data. In a separate registration database (a password protected Excel file), basic personal data like name, sex, date of birth, and where applicable, reasons for non-participation or lost to follow-up of potential participants (i.e. all clients referred to the trauma center for intake that are interested in participation) is stored. The registration database supports the planning of all assessments and is stored on a separate account accessible only to the research nurses. The registration database includes the key to the anonymized data. For the analyses, an anonymized dataset is extracted from the online questionnaire system RoQua (Routine Outcome and Quality Assessment). Data collected specifically for the present study that cannot be stored in the RoQua system, is stored on separate, anonymized (SPSS, Word and MPEG-4 Audio) files. This concerns the treatment history questionnaire and the qualitative interviews. During data collection and analysis, data files are only accessible for the research nurses during data collection. After terminating data collection, the researchers involved in the project can access the anonymized data file. The only exception are the qualitative interviews, which the interviewing researchers (PV and AK) can access during the study.

The datasets of this study will not be publicly available because they contain personal information. Access to the dataset is restricted to project team members. The processed and pseudonymized data can be obtained from the principal investigator upon reasonable request, provided the research question aligns with the informed consent. Study results will be published in international peer-reviewed journals and presented at conferences, regardless of the outcomes.

### Sample size calculation

2.8

Seven paired-samples t-tests are used to assess short term within-subjects differences in 1. PTSD severity (measured with the CAPS-5 and PCL-5 scores); 2. BPD severity (measured with the BPDSI total score and sum score of subscale Parasuicidal of the BPDSI) and 3. dissociation (measured with the SDQ-20, DES and sum scores of items 19 and 20 of the CAPS-5). To correct for chance capitalization as a result of multiple testing we use a conservative alpha level of 0.01, thereby lowering the chance of a type 1 error. We choose a power of.80. The minimum needed sample size, based to detect a medium difference (of 0.5 SDs) between the two paired scores is N=51 (using G*power) with α=.01 and a power of.80. We anticipate a minimal dropout of about 10%. This is based on the smaller drop-out rates in the RCT of Bohus et al. (2013), in combination with the naturalistic design of the current study which may involve more drop-out. We compensate for possible missing values or loss to follow-up by including an extra 10%, yielding a total sample size of 56 clients.

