#### Primary outcome: PTSD

2.6.1

The Life Events Checklist-5 (LEC-5) (37, 38) is a self-report measure that assesses type of trauma. It consists of 16 traumatic events that may lead to PTSD. The LEC-5 is administered a as part of regular diagnostics.

With the Clinician Administered PTSD Scale for DSM-5 (CAPS-5) (39, 40) we measure the presence and severity of PTSD. The CAPS-5 has a range of 0-80 with higher scores indicating more severe PTSD symptoms. In the last week of treatment the week-version of the CAPS-5 is standardly used at the treatment Centre to assess PTSD posttreatment (T2). The CAPS-5 has high interrater reliability (ICC = .98) and internal consistency (α = .90) for measuring PTSD severity. Based on considerations expressed by Larsen et al. (41) and Varker et al. (42), we define treatment response as a decrease of ≥9 points (11%) on the CAPS-5, remission as a CAPS-5 score of <12 and sustained PTSD remission at 6 and 12 months follow-up.

We use the PTSD Checklist for DSM-5 (PCL-5) (43) to assess the self-reported severity of PTSD. This questionnaire consists of 20 items with a 5-point Likert Scale (0-4) and has a range of 0-80. It is sensitive to measure change in PTSD symptoms and has good psychometric properties (43, 44).

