#### Dissociation

2.6.2

Dissociative experiences are assessed with the Dissociative Experience Scale (DES) (45), a self-report questionnaire that consists of 28 questions (range of 0-100). Items are scored on a Likert-scale varying from 0% (never) till 100% (all the time). Reliability and validity have been confirmed (45, 46).

The Somatoform Dissociation Questionnaire-20 (SDQ-20) (47, 48) is a self-report questionnaire that assesses somatoform dissociative symptoms. Two studies demonstrated convergent and criterion-related validity and high internal consistency in Dutch samples (47). Third, we assess the dissociative subtype (depersonalization and derealization) with two items (range of 0-8) of the CAPS-5.

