#### Short and long term effects of DBT-PTSD

3.1.1

To study short-term within-subjects differences, change scores will be calculated with the first three time points (T2-T1=Δtreatment and T1- T0=Δwaiting-list), resulting in four Δ-variables for PTSD, six for dissociation, two for NNSI and suicidal ideation and two for borderline symptomatology. Two-sided paired-samples t-tests will be conducted to compare the Δtreatment and Δwaiting-list scores. We use two-sided tests to maintain a conservative α level. When the anticipated waiting list period turns out to be less than three months, we will consider excluding the participant from the paired t-test analyses. When, at the end of the study, the waiting list period appears to vary much more than expected, and we might need to exclude too many patients, we will consider alternative statistical analyses that are able to deal with this variability, such as linear mixed model analysis. *Post-hoc* analyses to assess long term treatment effects in PTSD, dissociation, NNSI and suicidal ideation, and borderline symptomatology will be carried out with linear mixed model analyses with time as random effects. We will include two predictors of treatment effects on PTSD severity, as measured with the CAPS-5 and PCL-5 into the PTSD model: 1) baseline severity of BPD symptoms (using the total score on the BPDSI) and 2) cluster C personality disorders (with the sum of the dimensional SCID-5-P scores of the three cluster C personality disorders). Further, we will use linear mixed model analyses to study the effects of DBT-PTSD on social functioning and quality of life over time.

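### The CAPS-5 dissociation outcome is scored by item numbers that, under ordinary 1-to-20 numbering, belong to the PTSD severity total, and the article does not reconcile them with its definition by content

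*Protocol article*

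**What the plan says.** Three places in the protocol article bear on this outcome.

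- **Section 2.8 (Sample size calculation)** lists the variables to be tested. The third group, dissociation, consists of the SDQ-20, the DES and the "sum scores of items 19 and 20 of the CAPS-5". This is the only place where item numbers appear. The CAPS-5 severity score is listed separately, under PTSD.
- **Section 2.6.2 (Dissociation)** describes the measure by what it asks: "we assess the dissociative subtype (depersonalization and derealization) with two items (range of 0-8) of the CAPS-5". It gives no item numbers.
- **Section 2.6.1 (Primary outcome: PTSD)** gives the severity scale: "The CAPS-5 has a range of 0-80 with higher scores indicating more severe PTSD symptoms". It does not say how many items make up that range, how they are numbered, or whether the two dissociation items count in it. For the parallel self-report scale, the PCL-5, it does state the structure: "This questionnaire consists of 20 items with a 5-point Likert Scale (0-4) and has a range of 0-80".

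The outcome is used in the main short-term comparison. Section 2.8 says "Seven paired-samples t-tests are used to assess short term within-subjects differences", and section 3.1.1 counts the change scores, "resulting in four Δ-variables for PTSD, six for dissociation".

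**The concern.** One section defines the outcome by content and another by item number, and nothing shows that the two definitions pick out the same items. The score ranges suggest that they may not. A 0-80 scale with 4 points per item has room for exactly 20 items, and numbers 19 and 20 would ordinarily be the last two.

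The introduction makes the mismatch more likely. It describes PTSD symptoms as intrusions, avoidance, negative cognitions and mood, and hyperarousal, and it names dissociation separately among the problems that often accompany PTSD. On that account there is little reason to expect depersonalization and derealization among the severity items.

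What is at stake is the meaning of one result. The introduction hypothesizes that dissociation falls after treatment but not over the waiting period. If the syntax follows section 2.8 and the numbers are wrong, a fall in two PTSD symptoms would be published as a fall in dissociative-subtype symptoms. Nothing else in the article would reveal it.

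**Working it through.** **Place of the outcome in the plan.** Section 2.8 lists CAPS-5, PCL-5, BPDSI total, BPDSI Parasuicidal, SDQ-20, DES and the CAPS-5 item sum, which makes 7 tests as stated. Section 3.1.1 counts 4 + 6 + 2 + 2 = 14 change variables, and 14 / 2 periods = 7, which agrees. For dissociation, 6 / 2 = 3 measures. The item sum is therefore one of 7 tests, one of 3 dissociation measures and two of 14 change variables.

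**Sample size, reproduced first.** Inputs from section 2.8 are a difference of 0.5 SD, α = 0.01 and power 0.80; section 3.1.1 makes the tests two-sided. The smallest n for which the exact (noncentral t) power of a paired t-test reaches 0.80 is 51, with power 0.809. This matches the stated 51. With the extra 10%, 51 × 1.10 = 56.1, against the stated 56. The formula does not involve which items are summed, so correcting the item reference leaves both figures unchanged.

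**Item count implied by the ranges.**

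1. Points per item, from section 2.6.2: 8 / 2 = 4.
2. Items in the severity total, from section 2.6.1: 80 / 4 = 20, assuming that every severity item also runs 0-4.
3. Check against the structure stated for the PCL-5: 20 × 4 = 80. This is the same range.
4. If severity items are numbered 1 to 20, items 19 and 20 are the last two of them.
5. Points shared with the severity total in that case: 2 × 4 = 8, and 8 / 80 = 10%.

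**What follows under each reading of items 19 and 20.**

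| Reading | Agrees with section 2.6.2? | Points shared with the 0-80 total |
|---|---|---|
| (a) Two ordinary PTSD symptoms within the total | No: the score is not dissociation | 8 of 80 |
| (b) Depersonalization and derealization, within the total | Yes, but the items also count in the primary score | 8 of 80 |
| (c) Depersonalization and derealization, numbered so that they lie outside the total | Yes | 0 |

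Steps 1 to 3 rest on printed ranges and the assumption of equal item scoring. Step 4 rests on a numbering that the article does not print. Readings (a) and (b) need step 4; reading (c) denies it.

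**The case against.** The strongest reply is that the decisive step is inferred. The article never states the number of CAPS-5 items, their numbering or the wording of items 19 and 20. The 20-item structure is printed for the PCL-5 only. A score range cannot show where numbering starts or whether unscored items come between. On reading (c) nothing is wrong, and the text does not exclude it. This stands, and it is why the point is put conditionally. A reader might infer that the ranges by themselves place the items inside the total, or prove that the wrong construct will be scored. The documents do not support either step.

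A second reply is that overlap with the severity total is not in itself an error. Section 2.8 also tests the BPDSI total beside its own Parasuicidal subscale, and it nowhere says that the outcomes share no items. This stands too. Under reading (b) the score would still measure dissociation, and the shared points would need disclosure, not removal.

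A third reply is that section 2.6.2 fixes the construct, so an analyst may pick the right items by content. That is possible, but section 2.8 is where the tested variable is specified, and item numbers are what goes into scoring syntax. The two sections still need to agree.

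Finally, the DES and SDQ-20 also measure dissociation, and the introduction lists dissociation as a secondary outcome. This limits the consequence but does not remove the inconsistency.

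**Conclusion.** The point holds as an unreconciled definition. The content definition in section 2.6.2 and the item numbers in section 2.8 are not shown to match, and under ordinary numbering the named items fall inside the 20 severity items that the ranges imply. The introduction's separation of dissociation from the core PTSD symptoms makes reading (a) the more likely of the two problem readings. In that case one of seven tests would carry the wrong label. In reading (b) the only consequence is that 10% of the primary severity range is shared.

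The conclusion assumes that every severity item scores 0-4 and that the severity items are numbered 1 to 20. If the second assumption fails, the numbers may be correct and only the explanation is lacking. The article also gives no basis for asserting that the dissociation items lie outside the 0-80 total; it simply does not say. The sample size, the other six tests and the other two dissociation measures are unaffected.

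**What to change.** 1. Check items 19 and 20 against the CAPS-5 form used in the study, including the week version that section 2.6.1 says is used at posttreatment.
2. Define the outcome in section 2.8 by content (depersonalization and derealization), with the item numbers that match on that form, and repeat those numbers in section 2.6.2.
3. State in section 2.6.1 or 2.6.2 whether the two items count in the 0-80 severity total. If they do, say so when both results are reported.
4. Compare the scoring syntax with the corrected definition before any analysis is run.

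The cost is a line or two of text and a syntax check. No new data are needed, and the sample size stays at 51 (56 with the allowance).

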Although clients with PTSD after childhood abuse do benefit from evidence-based treatments (17, 18), there is room for improvement. For one, pooled drop-out rates vary between 16% and 41.5% (19, 20), appear to be greater in trauma-focused therapies and with childhood abuse-related PTSD (19, 21). Further, symptoms seem to improve to a lesser extent after interpersonal trauma (22), for clients with complex PTSD after childhood (sexual) abuse (23) and for clients with comorbid personality disorders (24). Also, emotion regulation and quality of life do not automatically improve after PTSD treatment, as shown in a systematic review and meta-analysis (18). For example, women with PTSD after childhood trauma reported very modest quality of life improvements that moved from ‘very low’ before Cognitive Processing Therapy to ‘low’ afterwards (5). Recently, more integrated and personalized interventions were suggested to improve treatment results (25, 26).

One such approach is the integration of Dialectical Behaviour Therapy (DBT) and Prolonged Exposure (PE). Several groups have studied a combination of PE and DBT, to make PTSD treatment accessible for clients with complex psychopathology, including high-risk behavior (27), and to address the needs of clients with chronic PTSD after childhood sexual abuse (28, 29). A systematic review and meta-analysis of inpatient and outpatient treatments that combine DBT and PE finds that PTSD and depressive symptoms decrease (30). Steil et al. (2011) developed inpatient DBT-PTSD for clients with severe PTSD after childhood sexual abuse. This treatment program of 12 weeks is based on DBT principles, includes PE as primary trauma-focused intervention and incorporates elements of Acceptance and Commitment Therapy and Compassion Focused Therapy (31). In a pilot (N=29) and RCT (N=74), with a Treatment As Usual (TAU) waiting list condition, women with and without comorbid BPD reported significant and clinically relevant improvements in PTSD after inpatient DBT-PTSD (28, 29). Drop-out was low in both RCT groups (DBT-PTSD: N=2, 5.5%; Control: N=3, 7.9%). Finally, in an observational study clients reported more improvement in PTSD symptoms, dissociation and disturbances in self-organization after inpatient DBT-PTSD than those treated with an inpatient TAU that included group interventions and trauma-focused treatment (32).

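### The 56 clients in section 2.8 fall just short of the stated 51 pairs: adding 10% does not offset a 10% loss, and the allowance does not count loss over both study periods

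*Protocol article*

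**What the plan says.** Section 2.8 (Sample size calculation) sets the test level, "we use a conservative alpha level of 0.01", and the target, "We choose a power of.80". It gives the requirement for a "medium difference (of 0.5 SDs) between the two paired scores is N=51". On attrition it says "We anticipate a minimal dropout of about 10" per cent. It explains that this rests on the lower rates of the inpatient DBT-PTSD RCT, together with the naturalistic setting, which may lose more. The allowance is then made by "including an extra 10%, yielding a total sample size of 56 clients".

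The RCT rates are in the Introduction: "Drop-out was low in both RCT groups (DBT-PTSD: N=2, 5.5%; Control: N=3, 7.9" per cent. That trial had parallel arms, with a treatment-as-usual waiting list as control.

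Section 3.1.1 describes the analysis: "Two-sided paired-samples t-tests will be conducted to compare the Δtreatment and Δwaiting-list scores". The treatment change is T2 minus T1 and the waiting-list change is T1 minus T0.

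**The concern.** Two things in section 2.8 do not fit together.

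First, the allowance is a multiplication. Raising a requirement by 10% does not protect it against a 10% loss, because the loss is taken from the larger number.

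Second, the allowance is meant to exceed the RCT's loss, but the RCT rates describe arms that were each followed over one period. A client here contributes a complete pair only if assessed at T0, T1 and T2, that is, through the waiting list and then through treatment. A rate for one period understates the loss over two.

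At stake is whether the stated 56 delivers the stated 51 pairs and so the stated power of .80.

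**Working it through.** **Inputs.** Section 2.8: alpha .01, power .80, difference 0.5 SD (read as a standardised paired difference of 0.5), loss about 10%, total 56. Section 3.1.1: two-sided paired t-test on change scores that need T0, T1 and T2. Introduction: RCT loss 5.5% (treatment) and 7.9% (waiting list).

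**Reproducing the plan's figures.** Exact noncentral-t power for a two-sided paired t-test at alpha .01 with a standardised difference of 0.5 first reaches .80 at 51 pairs, where it is 0.809. So 51 is right. The total is 51 × 1.10 = 56.1, stated as 56.

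**Check 1: does 56 survive a 10% loss?**
- 56 × (1 − 0.10) = 50.4 pairs. Power at 50 pairs is 0.799.
- Largest loss that still leaves 51: 1 − 51/56 = 0.089, or 8.9%.
- Inflation by division: 51 / 0.90 = 56.7, so 57.

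**Check 2: loss over both periods at the RCT's own rates.**
- Retention through waiting list and treatment: (1 − 0.079) × (1 − 0.055) = 0.921 × 0.945 = 0.870.
- Combined loss: 1 − 0.870 = 13.0%.
- Complete pairs from 56: 56 × 0.870 = 48.7, about 49. Power at 49 pairs is 0.789.
- Using counts gives the same answer. Arm sizes of 36 and 38 are inferred from the percentages and the RCT total of 74: (34/36) × (35/38) × 56 = 48.7.

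**Summary, with one sensitivity value.**

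| Loss T0 to T2 | Complete pairs from 56 | Power |
|---|---|---|
| 8.9% (most that 56 can absorb) | 51 | 0.809 |
| 10% (stated) | 50 | 0.799 |
| 13.0% (RCT rates in sequence) | 49 | 0.789 |
| 16% (sensitivity only) | 47 | 0.767 |

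The 16% is the lower end of the range in the Introduction, where "pooled drop-out rates vary between 16% and 41.5" per cent.

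**The case against.** The strongest reply is that nothing material is wrong. The text says an extra 10% was added, and it was. The loss is given only as approximate, 57 is one client more than 56, and 0.799 rounds to .80. Even at 49 pairs power is about one point below target, well inside the uncertainty of a conventional medium effect. This stands, and it is why the point is minor. It does not make the statement correct: at the loss it names, 56 does not leave 51 pairs.

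A second reply is that the sequential calculation leans on a trial the reader cannot see. The article does not say whether drop-out there meant leaving treatment or missing an assessment, and its waiting-list arm consisted of allocated controls. Clients here have committed to the programme and are waiting for a place in it. That is fair, and the 13% is conditional on those rates transferring. But section 2.8 chose this trial as its basis and intended to exceed its loss, so the rates should be applied to the periods a client actually passes through.

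A third reply is that analysis is by intention to treat and multiple imputation is intended (sections 3.1 and 3.2), so clients with a missing T2 may stay in. This also holds in part. Stopping treatment need not mean a missing T2, and 49 is a count of complete pairs rather than the analysed number. But imputation is conditional in the plan and does not restore all the missing information.

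Two stronger readings are tempting, and the article does not support either:
- **That the broader population here implies more drop-out than in the RCT.** The Introduction links higher drop-out to childhood abuse-related PTSD, which is the RCT's own population. Nothing in the article ties drop-out to gender, and section 2.8 already raises the RCT rates for the naturalistic setting.
- **That power will fall to about 0.70 or 0.56.** Those values follow from 25.5% loss (56 × 0.745 = 41.7, about 42 pairs) and 41.5% loss (56 × 0.585 = 32.8, about 33 pairs). The first rate is for outpatient DBT-PTSD (Discussion). The second is the top of the pooled range across PTSD treatments. Neither describes this inpatient programme, for which the article reports low drop-out.

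**Conclusion.** The point holds as a minor one. The 51 is correct, but 56 does not deliver it at the stated loss (50.4 pairs, power 0.799 at 50). At the RCT's two rates in sequence, complete pairs fall to about 49 and power to about 0.79. The allowance meant to exceed the RCT's loss is therefore below it once both periods are counted. The size is one to two pairs and about one percentage point below .80.

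The first part rests on arithmetic alone. The second assumes that losses in the two periods are independent, that the RCT arm rates carry over, and that a client who drops out lacks the later assessment. Section 3.1.1 also allows clients who waited less than three months to be left out of the paired tests. That loss is not identified in the 10% and cannot be sized from the article.

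A reader might infer that the study is seriously underpowered or must recruit more. These figures do not show that.

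**What to change.** Restate the attrition part of section 2.8:
- Define expected loss as loss of a complete T0, T1, T2 set, covering the waiting list and treatment together.
- Inflate by dividing by (1 − d), where d is that loss, and drop the implication that an extra 10% offsets a 10% loss (51 / 0.90 = 57).
- State that 56 clients are expected to yield about 49 to 50 complete pairs, with power about 0.79 to 0.80, and name the assumptions.
- If a higher loss is shown, label it as sensitivity only (for example 16%: 47 pairs, power 0.77).

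The cost is a few sentences and a very slightly less favourable power statement. The sample size, design and analysis stay as they are, and no extra clients are required.
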